**Figure 2 F2:**
[figure not shown]
Traditional and remote clinics and data capture points.

### Quantitative analysis

Quantitative analysis will examine patient characteristics, symptom resolution, discharge rates, consultant review volumes and waiting times, as well as environmental sustainability (assessed by the carbon footprint of clinics and patient travel).

Acceptability will be gauged using a 5-point Likert scale and open-ended questionnaires. Descriptive statistics (means, SD and CIs) will summarise continuous data, while discrete variables will be reported as counts and percentages. Standard regression models (95% CIs) and subgroup analyses will compare groups, with outcomes reported in scoring scales analysed as continuous variables. Count models will be used to count outcomes (such as number of appointments) and time-to-event models to assess time to definitive treatment/decision. A 5-point Likert scale questionnaire will further capture how different clinic permutations align with patient expectations. Missing data will be handled initially by descriptive means, aiming to describe the proportion of missing data, its characteristics and potential mechanisms and then using multiple imputation methodology. Analyses will adjust for age, sex, IMD quintile, baseline symptoms, presenting condition category, comorbidity count and distance to clinic; robustness will be checked using propensity score weighting. Differential follow-up will be handled with time-to-event methodology, using Cox proportional hazards, accounting for the differences in the follow-up duration across groups with different pathology.

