### Secondary outcomes

Clinical throughput impact:Investigate impact of remote pathway on waiting times from referral to treatment.Compare the clinician time required per remote consultation to reach diagnosis/definitive treatment.Stakeholder acceptability:Examine barriers to implementation, training needs, scalability and throughput.Determine the optimal setting for data capture and assess geographic variation.Assess the impact across different demographics, especially under-served populations.Health economic analysis:Conduct a cost-consequences analysis detailing waiting times, quality of life, resource use, costs, time off work and productivity for both study groups.Perform cost-consequence and cost-utility analyses from an NHS perspective.Environmental sustainability:Calculate the direct (patient journey) and indirect (clinic output) carbon footprint of the ENT outpatient service by assessing carbon dioxide equivalents (CO_2_Eq) for both new and existing clinic models by location.

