### Recruitment

Patients referred from primary care to ENT specialist services and attending either a conventional face-to-face consultant-led clinic or a remote clinic will be recruited into the study. We will send an invitation letter explaining the purpose of the study to the patients, along with their clinic invitation letter, and potential participants will be approached prior to their initial clinic appointment.

On their attendance at clinic, patients will be approached by a member of the healthcare team and will be given the study information package and offered the opportunity to ask questions and discuss their potential participation in the study. For those patients who agree to take part, this will be documented in their medical records and the research team will begin informed consent procedures.

Patients will not be randomised, and the study will not have any influence on the allocation of patients to the traditional or the remote pathway, which will be arranged by UHB, on a weekly basis, according to clinical priority and waiting length per referral. The clinic allocation process is regulated by the hospital and patients are allocated in consecutive order to either a face-to-face or a remote clinic, until all the slots of that week have been filled, before booking patients for a different week. Patient prioritisation is made in the form of urgency, without reference to the method of clinic delivery. Patient demographics, disease severity or other characteristics are not used in regards to allocation to an in-person or remote clinic appointment.

This will ensure that selection bias will not be introduced on the patients seen in the remote pathway, compared with the cohort seen face-to-face. We will assess propensity scores for the patients and assess their propensity score weighting using logistic regression.

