This is an observational study, and we are not measuring the effect of an intervention. Our initial sample size calculations have been driven by similar pieces of implementation studies in the literature, looking into studies assessing non-inferiority interventions for remote/telehealth clinics, as well as assessing the potential financial benefit to the patients/service and the environmental impact,^11^,^15^ further informed by similar studies mapped through our team’s scoping review.^6^ Continuous sampling will be undertaken on both pathways until we reach a number of 150 participants from each group that have completed the initial questionnaires. The patients of the remote pathway will also be sent a follow-up questionnaire after their discharge, asking for their overall experience of the new service. The total of recruited participants will be expected to exceed the minimum of 300 we need for our analysis, and we will be allowing for a 10% attrition, as the current number for patients seen in face-to-face and remote clinics exceeds the 80 patients per cohort, per week. All the primary outcomes data will be extracted directly from the clinical notes of the patients, while the data of the secondary outcomes will be procured via questionnaires.

For the interviews, we will use a topic guide developed based on the existing literature and the research team’s experience of technology and innovation implementation, as well as service redesign.^16^,^18^ Through the interview process, we will investigate the experience of the different stakeholders involved in the remote pathway. We will undertake purposive sampling to select participants, expecting 30–35 participants in total, to allow for thematic saturation to take place.^19 20^ Participants in the interviews will be classified into two categories: patient participants and NHS staff. Recruitment will continue until overall thematic saturation has been achieved within each group. Patients enrolled will be approached, after completing the remote clinic pathway, while clinicians, managers and the other stakeholders will be given participation leaflets and invited via email or in person to participate in the study through interviews. If non-English speakers participate in the interviews, interpreters will also be facilitating the process.

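### The pathway comparisons make no provision for patients sharing a clinic session or a deciding consultant, so their 95% CIs may be too narrow

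*Protocol article*

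**What the plan says.** The analysis is set out in the protocol article under Quantitative analysis: "Standard regression models (95% CIs) and subgroup analyses will compare groups". For other outcome types, "Count models will be used to count outcomes (such as number of appointments) and time-to-event models to assess time to definitive treatment/decision". The adjustment set follows: "Analyses will adjust for age, sex, IMD quintile, baseline symptoms, presenting condition category, comorbidity count and distance to clinic". Propensity score weighting is the robustness check, and Cox models handle differential follow-up. All seven covariates describe the patient. Session, site and consultant appear neither as model terms nor as a basis for the standard errors.

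The grouping is described elsewhere. Under Recruitment, "patients are allocated in consecutive order to either a face-to-face or a remote clinic", with the week's slots filled before the next week is opened, so everyone in a given clinic has the same pathway. The Introduction and Project setting explain that trained staff collect the data in remote clinics and that ENT consultants then review it and decide diagnosis and management.

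Several outcomes depend on clinicians' decisions or working style. The number of appointments to definitive treatment is listed under Primary outcome. Secondary outcomes include "Compare the clinician time required per remote consultation to reach diagnosis/definitive treatment". Discharge rates and time to definitive treatment or decision appear under Quantitative analysis.

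Sampling runs "until we reach a number of 150 participants from each group that have completed the initial questionnaires".

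**The concern.** Whether a patient is discharged, followed up or given a final plan at the first visit depends partly on who decides. If consultants have different thresholds, patients of the same consultant resemble one another. Patients in the same session may also share staff, equipment and setting. Because pathway does not vary within a session, any session-level variation goes straight into the error of the pathway contrast. The same holds for consultant-level variation if each consultant works in only one pathway.

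The models as named, run with their usual standard errors, would count each patient as a separate piece of evidence. Differences between a small number of sessions or decision-makers could then be reported as a pathway effect with an interval that looks more precise than it is. Adjusting or weighting on patient characteristics does not remove this, because the variation lies with the clinic or clinician. At stake are the clinician-driven efficiency comparisons.

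**Working it through.** **The plan's own figure.** The only relevant figure is 150 per group. It cannot be reproduced, because the basis given is that "Our initial sample size calculations have been driven by similar pieces of implementation studies in the literature" and no alpha, power, effect, SD, margin or design effect is stated. The calculation below therefore takes 150 as given and asks what clustering would do to it.

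**Inputs from the article.** n = 150 per group (Recruitment). The pilot proportion managed remotely is 83% (Introduction), used here only to illustrate interval width.

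**Assumed inputs, not in the article.** ICC 0.01 to 0.10; m = 5, 10 or 15 study participants per cluster, which is 30, 15 or 10 clusters per pathway.

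**Case 1: clusters nested in pathway.**
- Design effect: DE = 1 + (m − 1) × ICC
- Actual coverage of an interval with ordinary standard errors: 2Φ(1.96/√DE) − 1
- Effective sample size per group: 150/DE

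| m | ICC | DE | Coverage | Effective n |
|---|---|---|---|---|
| 5 | 0.01 | 1.04 | 94.5% | 144 |
| 5 | 0.05 | 1.20 | 92.6% | 125 |
| 5 | 0.10 | 1.40 | 90.2% | 107 |
| 10 | 0.01 | 1.09 | 94.0% | 138 |
| 10 | 0.05 | 1.45 | 89.6% | 103 |
| 10 | 0.10 | 1.90 | 84.5% | 79 |
| 15 | 0.01 | 1.14 | 93.4% | 132 |
| 15 | 0.05 | 1.70 | 86.7% | 88 |
| 15 | 0.10 | 2.40 | 79.4% | 62.5 |

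Two cases lie outside this range. With m = 2 and ICC 0.01, DE is 1.01 and coverage 94.9%, which is negligible. With m = 30 (for example 5 consultants per pathway, 150/30) and ICC 0.10, DE is 3.90 and coverage 67.9%.

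**What this means on a familiar scale.** At 83%, the ordinary half-width for a difference is 1.96 × √(2 × 0.83 × 0.17/150) = 8.5 percentage points. At DE 1.45 it should be 8.5 × √1.45 = 10.2 points. For a single group of 150, 1.96 × √(0.83 × 0.17/150) = 6.0 points becomes 7.2.

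**Case 2: consultants working equally in both pathways.** The consultant effect cancels from the difference, so the true variance is (1 − ICC) times the ordinary one. Coverage is 2Φ(1.96/√(1 − ICC)) − 1: 95.1% at ICC 0.01, 95.6% at 0.05 and 96.1% at 0.10. The ordinary interval is slightly too wide. Sessions remain nested in pathway in this case as well.

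**How large clusters could be.** Current flow is above 80 patients per cohort per week. If every patient took part, 150 would be reached in 150/80 = 1.9 weeks, and participants would come from few sessions. Uptake is not stated, so this shows only that sizeable clusters are possible.

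**The case against.** The strongest reply is that the concern argues from silence. The article nowhere says that patients are treated as independent, and standard regression does not rule out random effects or robust standard errors. An article condenses the full plan, and an analysis plan that is not shown may deal with the point. This has weight. It does not dispose of the point, because the section is specific about everything else: model families, imputation, seven named covariates and weighting. Followed literally, it gives an analysis that ignores sessions and consultants.

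A reader might infer more than the article supports. Five stronger readings fail:

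- *That the 95% CIs are wrong.* Size and direction depend on the ICC, the cluster size and whether consultants work in both pathways, none of which is given. The error ranges from negligible or slightly conservative to serious.
- *That shared sessions prove correlated outcomes.* The grouping follows from the article; the correlation is plausible but not shown.
- *That session and consultant are the same unit.* In the remote pathway consultants review the data afterwards and flexibly. Patients from one session may have different reviewers, and one reviewer may cover many sessions.
- *That settings are nested in pathway.* Project setting lists hospital outpatients, diagnostic hubs and primary care clinics without assigning each to one pathway.
- *That all primary outcomes are affected through the quoted comparison.* The proportion managed after a single remote consultation and the re-presentation rate are remote-group quantities. Of the primary outcomes, only the number of appointments could be a pathway contrast. Clustering can still narrow the interval of the remote-only proportion, but the sentence on group comparisons does not govern it.

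It can also be argued that in a single-centre evaluation the consultants are part of the service under study rather than a sample from a wider group. That is a legitimate choice of target, but it should be stated, and it leaves session-level variation untouched.

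**Conclusion.** The point holds as a conditional one. The article fixes pathway at clinic level, has consultants deciding for many patients, and names pathway analyses that account for neither. If clinician-driven outcomes correlate within session, or within consultants who work in one pathway, the 95% CIs for the pathway comparisons may be too narrow.

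Under the assumed ICC of 0.01 to 0.10 and 5 to 15 participants per nested cluster, true coverage runs from 94.5% to 79.4%, and 150 per group is worth between about 144 and 62 independent patients. With consultants split evenly across pathways, the consultant component gives 95.1% to 96.1%. These figures rest on equal cluster sizes and on ICCs and cluster sizes that the article does not supply. They show a range of possible error, not a demonstrated one.

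**What to change.** Make four changes to the analysis text and the data extraction:

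1. Extract clinic session and reviewing consultant for every participant, along with the primary outcome data that already come from the clinical notes. The article does not say that these identifiers are in the notes, so this should be checked before recruitment is far advanced.
2. State whether consultants serve both pathways, and the expected number of sessions and consultants in each.
3. Account for clustering in all pathway comparisons, including the count, Cox and propensity-weighted analyses. If consultants work in both pathways, include a consultant effect. Otherwise use cluster-robust or mixed-model standard errors at the highest level nested in pathway. Apply a small-sample correction when clusters are few.
4. Use the same approach for the CI of the remote-only proportion managed after one consultation.

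The cost is small: two more identifiers per participant and a few sentences in the plan. The downside is that intervals will probably be wider if consultants are nested in pathway. If consultants work in both pathways, modelling them removes between-consultant noise from the comparison.

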## Introduction

 In 2009 the NHS Constitution set the standard of 92% of patients waiting no longer than 18 weeks from referral to treatment.^1^ In December 2024, 7.5 million patients in England were waiting for an appointment, with more than two-fifths waiting beyond the NHS standard.^2^ That proportion varies by speciality, with ear, nose and throat (ENT) demonstrating the worst waiting times, with over half of the patients exceeding the 18-week target.^1^

Hearing and ear problems, alongside nasal symptoms, are common in primary and secondary healthcare, with ear pain, discharge, recurrent infections, chronic rhinosinusitis and allergic rhinitis particularly common. While primary care management may suffice, many patients need specialist ENT referrals for diagnosis and management. However, lengthy waits, often exceeding twelve months, are commonplace for specialist consultations.^3^ This equates to over half a million patients having increased time spent with disease, distress and also potentially a poorer prognosis. Recent evidence suggests ENT patients are more commonly managed with advice, medications and then discharge, when compared with specialities such as orthopaedics or gynaecology with a higher proportion converting to surgical intervention,^4^ indicating that they can be effectively managed with fewer appointments and occasionally, entirely remotely.

Responding to the delays facing patients, a digitally empowered, remote ENT system has been developed by our team of collaborators, capitalising on advances in endoscopic nasal and ear imaging and boothless hearing tests. A pilot study, comprising 53 patients, demonstrated that 83% of cases could be effectively managed remotely via this service, with high levels of satisfaction reported by both patients and general practitioners.^5^

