**Figure 1 F1:**
[figure not shown]
Traditional and remote clinic pathways infographic. ENT, ear, nose and throat.

Our team has conducted a review of the literature to inform and guide the design of this study.^6^ Despite evidence supporting the feasibility and safety of digitally enabled remote ENT clinics, no consensus exists on the ideal placement of such a service. Moreover, there is still a need to further understand this pathway’s real-world effectiveness and acceptability across different stakeholders (patients, clinicians, managers), compared with the traditional face-to-face consultation model. Moreover, we need to investigate whether there are any specific groups of patients that such a digitally empowered pathway would work better for compared with others. Furthermore, aligning with the NHS net-zero agenda, we need to understand whether RAPID ENT could contribute to the reduction of the carbon footprint of the ENT outpatient care delivery.

Our research focus will evaluate the clinical and cost-effectiveness, acceptability and environmental sustainability of the remote clinics model, compared with the traditional pathway. This study is due to launch in October 2025 and will be undertaken for a period of up to 2 years, with October 2027 being defined as the end date of the study. The end of the study will be the date of the last follow-up and data collection via questionnaires and interviews of patient-participants, post the completion of their treatment. Documents will be archived following the University of Birmingham (UoB) Code of Practice for Research.

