### Inclusion criteria

Patient participants: patients referred from primary care, adults (18 years of age or older), with conditions of the ears or nose.

Non-patient participants: stakeholders with previous or current experience in digital or service transformation, stakeholders engaging in the implementation or delivery of the remote-enabled ENT clinical service.

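### The seven-variable adjustment set is too large for ordinary logistic regression on successful remote management, if that outcome is modelled within the remote arm

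*Protocol article*

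**What the plan says.** Under Quantitative analysis the article states that "Standard regression models (95% CIs) and subgroup analyses will compare groups" and that "Analyses will adjust for age, sex, IMD quintile, baseline symptoms, presenting condition category, comorbidity count and distance to clinic". Neither sentence is limited to particular outcomes. The same section gives count outcomes a count model, time to definitive treatment a time-to-event model, and scale scores a continuous-outcome analysis. A binary outcome therefore falls to standard regression with the full list. Propensity score weighting is planned as a robustness check.

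Under Primary outcome, successful remote management is a yes/no status defined for remote patients after one remote consultation, and the stated target is the proportion who achieve it. Re-presentation among remote patients is listed there too.

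Recruitment continues "until we reach a number of 150 participants from each group that have completed the initial questionnaires". The Introduction reports that "A pilot study, comprising 53 patients, demonstrated that 83% of cases could be effectively managed remotely via this service" and sets as a research need to learn "whether there are any specific groups of patients that such a digitally empowered pathway would work better for".

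**The concern.** To find out which patients the pathway suits, one must relate patient characteristics to success or failure among remote patients. The natural model is a logistic regression with the stated covariates. Its information is governed by the number of failures, which will be small if the service performs as in the pilot. With few failures per parameter, maximum likelihood pushes odds ratios away from 1. It can also break down through separation, where a covariate pattern contains no failures or only failures and the estimate is infinite.

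The risk is that some characteristics would look more strongly linked to failed remote management than they are, with less precision than the data allow. An adjusted analysis of smaller groups might give no usable answer.

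**Working it through.** **Inputs from the article.** Remote participants: 150 (Recruitment). Pilot: 53 patients, 83% success (Introduction). Seven covariates (Quantitative analysis).

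**Pilot figure.** 44/53 = 83.0%, so the stated percentage reproduces. The exact (Clopper-Pearson) 95% interval is 70.2% to 91.9%.

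**Expected failures.**
- At the pilot rate: 150 × 0.17 = 25.5.
- Across the pilot interval: 150 × (1 − 0.919) ≈ 12 to 150 × (1 − 0.702) ≈ 45.
- If the 10% attrition allowance raises recruitment to 150/0.9 ≈ 167 and all contribute: 167 × 0.17 ≈ 28.

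**Parameters.** Age 1 + sex 1 + IMD quintile 4 + baseline symptoms 1 + comorbidity count 1 + distance 1 = 9, plus k − 1 for k condition categories. The article does not state k. Patients have "with conditions of the ears or nose", so k = 2 is the minimum and gives 10. Assuming k = 4 gives 12. Linear age and a single symptom score are also assumptions.

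**Failures per parameter.** 25.5/10 = 2.6; 25.5/12 = 2.1.

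**Simulation, whole remote arm.** 150 patients, 17% failures, 12 parameters, assumed covariate odds ratios of 1.3 to 2.0, 2,000 datasets, maximum likelihood:

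| True odds ratio | Median estimate | Log-scale inflation |
|---|---|---|
| 2.0 (sex) | 2.24 | ln 2.24/ln 2 = 1.16, so 16% |
| 2.0 (an IMD contrast) | 2.21 | ln 2.21/ln 2 = 1.14, so 14% |
| 1.5 (age, symptoms) | 1.59, 1.57 | 14%, 11% |

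The two rows at 2.0 average about 15%. On the odds-ratio scale all four are about 5 to 12%. Coverage of the 95% intervals was 0.94 to 0.96, and 4% of fits gave no estimate.

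A further run compared estimators. Maximum likelihood inflated the log odds ratio by about 17% for a true value of 2, with 7 to 9% of fits non-estimable. Firth's method, with IMD kept as four parameters, removed the bias and always converged. Root mean squared error fell from 0.59 to 0.49, and (0.49/0.59)² = 0.69, so mean squared error fell by 31%.

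**Sensitivity to the failure rate.** With 150 patients, 50% of fits are non-estimable at 8% failures and 0.1% at 30% failures.

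**Full model refitted in remote-arm subgroups, 17% failures.** Non-estimable fits: 45% with 75 patients (about 13 failures), 79% with 50 (about 8) and 92% with 38 (6 to 7).

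**Both pathways, hypothetical.** If a matching outcome existed for all 300 patients at the same failure rate, there would be 300 × 0.17 = 51 failures for 13 parameters (3.9 each). A pathway odds ratio of 1.0 was estimated at 1.00. One of 2.0 (40 failures) was estimated at 2.10. At most 0.3% of fits failed.

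**The case against.** The strongest reply is that the article never commits to this model. Success is set as a proportion, discrete variables are to be reported as counts and percentages, and the regression sentence concerns group comparisons. Logistic regression is named only for the propensity score. This stands in part, and it is why the point is conditional on the outcome being modelled. But the adjustment sentence has no exception, and the question of which patients the pathway suits cannot be answered from the overall proportion.

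Four stronger readings are tempting, and the documents do not support them:
- **That the remote-versus-traditional odds ratio for success is inflated.** Success has no face-to-face counterpart, so no such odds ratio is defined, and in the hypothetical 300-patient version the distortion is small.
- **That every analysis is affected.** Number of appointments and time to definitive treatment have their own models.
- **That subgroup models will fail.** The article names no subgroup variable and no refit within strata; an interaction term or simple percentages fits its wording equally well.
- **That the under-served populations objective is lost.** Under Secondary outcomes that item sits within stakeholder acceptability, which is gauged on a Likert scale, with scale scores analysed as continuous.

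It is also fair that link functions and covariate coding are usually left to an analysis plan. Their absence is not the point here. The point is that the stated rule, followed as written, does not suit a sparse binary outcome. Propensity weighting does not help, because it balances pathways and this outcome exists in only one.

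**Conclusion.** The point holds in a limited form. An adjusted logistic model of successful remote management in 150 patients would have about 2 failures per parameter. For a true odds ratio of 2, ordinary maximum likelihood would overstate the log odds ratio by about 15 to 17%, and roughly 4 to 9% of fits would give no estimate. Interval coverage stays near 95%, so the damage is bias, lost precision and occasional non-estimation. Falsely narrow intervals are not the problem. The serious failure would arise only if the full model were refitted within remote-arm subgroups. The headline success proportion is untouched.

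The size rests on four condition categories, modest covariate effects and a pilot success rate from 53 patients. It also assumes that the pilot's notion of effective remote management matches the protocol's definition of success. With failures anywhere from 12 to 45, the problem ranges from half of fits non-estimable to almost none. No rate is given for re-presentation, so its sparsity cannot be sized.

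**What to change.** Add to Quantitative analysis:

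> Any adjusted model for successful remote management, or for another sparse binary outcome such as re-presentation, will use Firth penalised logistic regression, with the unadjusted result reported alongside. Subgroup results for these outcomes will be reported as proportions with exact or Wilson 95% intervals and will not be refitted with the full adjustment set.

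Entering IMD quintile as one linear term would save three parameters but is optional. It could hide an effect confined to one quintile, and Firth's method gives its gain with all four IMD parameters kept.

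No extra patients or data are needed. Odds ratios become slightly less extreme and subgroup figures are unadjusted. Penalised profile-likelihood intervals do not combine across multiple imputations by the ordinary Rubin's rules, so a pooling method must be chosen, which means a little extra analysis work.
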